## Abstract

**Background:**

Meta-analysis from previous studies have shown that treatment with mesenchymal stromal cell (MCSs) may increase the left ventricular ejection fraction (LVEF) after acute myocardial infarction (AMI) by 3.84%, and the effect is greater in those who are not aged and have developed a reduced LVEF. However, it seems that MSC transplantation does its effect through an indirect paracrine effect, and direct differentiation to the cardiomyocytes does not occur. Therefore, it can be hypothesized that this paracrine effect would be augmented if repeated doses of MSC are transplanted. This study is conducted to compare single vs. double injection of MSCs.

**Methods:**

This is a single-blind, randomized, multicenter trial aiming to determine whether intracoronary infusion of double doses of umbilical cord-derived Wharton’s jelly MSCs (WJ-MSCs) improves LVEF more after AMI compared to single administration. Sixty patients 3 to 7 days after AMI will be enrolled. The patients should be under 65 years old and have a severe impairment in LV function (LVEF < 40%). They will be randomized to three arms receiving single or double doses of intracoronary infusion of WJ-MSCs or placebo. The primary endpoint of this study is assessment of improvement in LVEF at 6-month post intervention as compared to the baseline.

**Discussion:**

This investigation will help to determine whether infusion of booster (second) dose of intracoronary WJ-MSCs in patients with AMI will contribute to increasing its effect on the improvement of myocardial function.

**Trial registration:**

Iranian Registry of Clinical Trials (www.IRCT.ir) IRCT20201116049408N1. Registered on November 26 2020

## Background

Myocardial infarction (MI), a common presentation of coronary artery disease, is the main cause of death in the developed countries [1]. Over the past few decades, a rise in the incidence of heart failure (HF) was observed in contrast to the reduction in the mortality rate after MI [2]. Occurrence of HF in hospitalized patients for an acute myocardial infarction (AMI) ranged from 14 to 36% in previous studies [3]. HF has an important impact on the healthcare system. HF accounts for 6 million patients, 300,000 death cases, and about $40 billion healthcare costs in the USA per year [4].

In spite of the current guideline-directed therapy [5], mortality and morbidity of post-MI heart failure is quite high [6, 7]. Although current managements for HF are prolonging the patients’ life while improving their symptoms, they do not restore the normal histologic architecture and induce regeneration in the damaged cells. Therefore, improving confirmed treatments and developing further approaches to treat patients with post-MI heart failure are strongly required [8]. One approach has pointed at stem cell-based therapies [9]. Cell therapy provides a potential approach to fundamentally reconstructing the dead myocardial cells.

### Cell-based therapy in cardiovascular disease

Cell-based therapy in cardiovascular diseases was initiated in the late 1990s when preclinical studies revealed the possibility of transplanting the skeletal myoblasts [10] and fetal cardiomyocytes [11] into ischemic myocardium. Afterwards, the bone marrow (BM) cell implant in murine models of MI was reported [12, 13]. Cell therapy moved forward to human studies with outstanding speed, using skeletal myoblasts in patients with HF in 2001 [14] and BM-derived cell transplantation in acute MI in 2002 [15]. Since then, many studies on animals and humans have been performed to assess different cell types and their ability to repair cardiac and vascular damage in the settings of MI, cardiomyopathy, etc.

### Mesenchymal stromal cells (MSCs)

MSCs are a population of cells initially isolated from the BM and have been found in other organs and tissues such as the heart, Wharton’s jelly, and adipose tissue [16]. Due to the availability of these resources, these tissues are becoming the dominant source for isolation of MSC for clinical uses [17]. Furthermore, the safety of MSCs-therapy from these origins has been confirmed previously [18]. Because of their desirable features, such as simplicity of isolation and ex vivo growth, in vitro stemness characteristics and an immune privileged feature, MSCs, are progressively used in clinical trials of stem cell therapy [19]. In the POSEIDON trial, it was shown that transplantation of allogenic as compared to autologous MSCs is completely safe and is equally effective [20]. In the TAC-HFT trial, it was shown that MSC are about twice as much effective as the bone marrow-derived mononuclear cells (BM-MNCs) [21]. Based on these findings, it seems that MSCs are the most readily available yet and efficient cells for regenerative therapeutic approaches in cardiology.

### Cell therapy in acute myocardial infarction

Most of the studies on cell therapy in AMI are done by BM-MNCs. Findings from those trials have cleared the path through other resources and answered many questions. Based on TIME trials, it was noticed that the best transplantation time after AMI is within 3 to 7 days just after the attack [22, 23]. Based on the meta-analysis by Fisher and colleagues, treatment with BM-MNC would increase left ventricular ejection fraction (LVEF) after AMI by 2.72%. It is of high importance to point that in the selected population of patients aged under 55 and LVEF under 37%, this treatment yielded survival and functional benefits as well [24].

Clinical trials using MSCs in AMI are controversial but encouraging. The largest clinical trial conducted in the field was done by Gao and coworkers on 116 patients. They found that umbilical cord Wharton’s jelly-derived MSCs could enhance the LVEF by nearly 5% [25]. A meta-analysis in the field showed similar results of improving LVEF by 3.84% [26]. These findings are parallel to the results of TAC-HFT trial that showed MSCs were nearly twice as much effective as BM-MNCs [21].

### Mechanism of action of cell therapy

The exact mechanisms accounting for the beneficial effects of using stem cells in HF in preclinical and clinical studies are not clear. The data supporting the theory on differentiation of the transplanted cells as a mechanism of improvement in the recipient heart are very poor; even if all of the remaining cells are transformed into the cardiomyocytes, it would not be sufficient to account for the useful effects reported [27]. Differentiation of the transplanted cells into new vessels has been observed in different cells, such as MSCs [28], and it has been suggested that vasculogenesis may result in rescuing the cardiomyocytes in the hypoxic area. It is challenging to imagine (consider) how the vasculogenesis mechanism could be a main mechanism in patients who already had successful coronary revascularization after an AMI; however, it is obvious that this phenomenon can be responsible for some of the advantageous effects of cell therapy. Recently, the paradigm has shifted from these mechanisms to the paracrine effect theory, which suggests that most of the beneficial effects after cell therapy are obtained through signals such as cytokines that are released in a paracrine signaling by the injected cells and alter the nearby cells and the recipient heart [29].

### Hypothesis generation

If the beneficial effects of MSC therapy could be explained by paracrine effect, increasing the frequency of cell injections would be associated with more useful effects on the recipient heart.

### Study design

This is a randomized, single-blind, multicenter phase II trial which aimed to determine whether the intracoronary infusion of double doses of the umbilical cord Wharton’s jelly tissue-derived MSCs as compared to one or no injection demonstrates greater effect on LVEF after an AMI when administered additionally to the standard management. This study has been approved by the “Ethics Committee of Shiraz University of Medical Sciences” (the code: IR.SUMS.REC.1399.406) and registered in the Iranian Registry of Clinical Trials website (https://www.irct.ir/) by the code IRCT20201116049408N1. The study protocol will be reported based on Standard Protocol Items: Recommendations for Interventional Trials (SPIRIT) guidelines (Online supplement 1). Figure 1 shows SPIRIT flow diagram of study.

**Fig. 1 Fig1:**
[figure not shown]
SPIRIT flow diagram of study

### Sample size determination

According to the objectives and type of the study and citing previous studies in this field, taking into account the 5% error, 90% power, 3% difference between placebo group and single dose injection group, and another 3% difference between single and double injection groups after the 6 month follow-up period and 1.3 standard deviation and 1:1:1 ratio, the sample size will be estimated in each group using the formula $$ n=\frac{2{s}^2{\left({z}_{1-\raisebox{1ex}{$\alpha $}\!\left/ \!\raisebox{-1ex}{$2$}\right.}+{z}_{1-\beta}\right)}^2}{{\left(\partial \right)}^2} $$ . Due to the length of the study and repeated measurements, using the formula $$ {n}^{\prime }=n\times \frac{1}{1-p} $$, and a drop of 15%, the sample size is decided 16 in each group. Finally, considering that in this study, three groups will be compared and according to the formula, $$ {n}^{\prime }=n\times \sqrt{k} $$, 20 subjects will be needed in each group, so a total of 60 patients will be selected. In the above formula, the values of *z* are constant and equal to 97.5th percentile and 80th percentile of the standard distribution. The ratio of people in the two groups and the effect size are the value divided by the standard deviation.

### Study participants

Sixty patients will be enrolled in this trial; they should have been hospitalized due to anterior ST elevation myocardial infarction (STEMI), undergone successful primary percutaneous coronary intervention (PCI), and had a LVEF < 40%. Centers participating in the trial are the Alzahra Heart Hospital (Shiraz, Iran), Nemazee Hospital (Shiraz, Iran), and Shahid Faghihi Hospital (Shiraz, Iran). Inclusion and exclusion criteria are listed below:

Inclusion criteria:
Ages 20–60 yearsGenders: BothFirst MI within 3 to 7 daysPost-AMI LVEF less than 40% as assessed by echocardiographyNegative pregnancy test (in women with childbearing potential)Written informed consent

Exclusion criteria:
History of prior anterior myocardial infarctionPatients with regional wall motion abnormalities in the non-infarct regionPrior coronary artery bypass graft (CABG) surgeryPatients with significant valve disease, defined as stenosis or regurgitation graded as greater than moderate (2+)Patients with another etiology of LV dysfunction (known/suspected non ischemic cardiomyopathy, previous anthracycline therapy, known ethanol abuse (greater than 6 oz. ethanol/day on a regular basis)Poor echocardiography windowActive infection or history of recurrent infection or positive test for syphilis (RPR), hepatitis B and C (HBsAg, Anti-HCV), HIV, and HTLV-1Documental terminal illness or malignancyPrevious bone marrow transplantAutoimmune disease (e.g., lupus, multiple sclerosis)

### Randomization and study blinding

Patients will be randomized 1:1:1 to receive WJ-MSCs using permuted block randomization with block size 6. The outcome assessors will be blinded to the assignment (single-blind). The randomization process will be done by using a web-based randomization service.

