### Intervention

The cGMP certified clinical-grad hWJ-MSCs produced by Cell Tech Pharmed Co. Ltd. (Tehran, Iran) are transported to the ward on the infusion day. The hWJ-MSCs were suspended in 0.9% normal saline. A qualified person will issue the certificate of analysis for each batch. The release of cells is in compliance with product specifications. The shipment will be handled considering validated standard operation protocols.

Forty patients in the two intervention arms will receive one intracoronary dose of 10^7^ WJ-MSCs infusion, and the control group will be administered only the conventional supportive treatment. For 20 patients among those who had received the first dose, the second dose of 10^7^ WJ-MSCs infusion was done within 10 days after the first injection.

A total of 60 patients in the three groups will be randomized in a 1:1:1 pattern to receive two doses of WJ-MSCs (*n* = 20; 2 × 10^7^ cells) or one dose of WJ-MSCs (*n* = 20; 1 × 10^7^ cells) in combination with conventional supportive treatments or conventional supportive treatments alone (*n* = 20).

When the cells are ready for infusion, the patients will return to the cardiac catheterization laboratory. The total number of 10^7^ WJ-MSCs will be infused via intracoronary route. If the activated clotting time is under 200, a weight-based bolus dose of heparin will be used.

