Therapeutic 6 Fr guiding catheter will be inserted into the left main artery. Two hundred micrograms of nitroglycerin will be infused via the guiding catheter. Angiography of LAD will be done, and TIMI flow will be documented. 0.014-inch soft-tipped guidewire wire will be inserted into LAD at distal edge of the stent. An over-the-wire balloon will be passed and placed within the stented area. It will be inflated to occlude the vessel. The guiding wire will be removed from the microinfusion device. Infusion syringe will be connected to the infusion catheter, and infusion of MSCs will be initiated at 2.5 ml/min. Occlusion with balloon catheter will be done using low pressure inflation (2–4 bar). Before each cell infusion, total occlusion of the coronary artery will be confirmed by injection of dye in the selected vessel. When one third volume of the cells is infused, the infusion pump will be ceased, and the contrast agent is injected into the guiding catheter to assess the TIMI coronary flow. This will be done again for the second one third volume. When cell infusion is completed, the coronary flow wire will be placed via the microinfusion catheter. After 10 days, this procedure will be repeated for patients in the third group.

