## Trial status

This trial is still recruiting the patients. Recruitment started on January 2021, and enrollment is estimated to end by November 2021. This protocol is version 2 approved on October 2020. The COVID-19 pandemics did not influence the patient enrollment in this trial.

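### A single block size of 6, disclosed during recruitment while treating staff can see who is infused, lets anyone who sees all earlier allocations on a list foresee part of the control-versus-cells sequence

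*Protocol article*

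**What the plan says.** The section on randomization and blinding fixes one method and one size: "permuted block randomization with block size 6". The ratio is stated as "Patients will be randomized 1:1:1 to receive WJ-MSCs", so each block holds two patients per arm. The sample-size section sets the total: "20 subjects will be needed in each group, so a total of 60 patients will be selected". That makes ten full blocks on a single list.

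On blinding, the same section says "The outcome assessors will be blinded to the assignment (single-blind"; no one else is named. On mechanism it says "The randomization process will be done by using a web-based randomization service".

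The Intervention section shows what treating staff can see: "the control group will be administered only the conventional supportive treatment". Patients in the cell arms return to the catheterization laboratory for balloon occlusion and infusion, and for the double-dose arm "After 10 days, this procedure will be repeated for patients in the third group".

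The Trial status section states "This trial is still recruiting the patients". Three hospitals in one city take part. The article does not say whether there is one list or one per centre, or who learns of earlier allocations.

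**The concern.** With a fixed and known block size, past allocations reveal what is left in the current block. The web service hides the next assignment but cannot prevent that deduction. Here the deduction is easy for the main distinction, because a patient either is or is not taken for infusion.

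Selection bias would enter at enrolment. Patients are eligible from day 3 to day 7, and consent is sought once they are judged stable, so staff have some discretion over whether and when to approach a patient. If staff expect the next slot to be control, or to be cells, they could hold back or bring forward patients with better or worse expected recovery of LVEF. Blinded reading of images protects the measurement but not the choice of who enters each arm. The comparisons at stake are single dose versus control and double dose versus control.

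**Working it through.** **Inputs.** Block size 6, three arms at 1:1:1, 60 patients (Protocol article, randomization and sample-size sections). The protocol gives no predictability figure to reproduce. A block has 6!/(2!·2!·2!) = 90 distinct orders, all equally likely.

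**Case A: the observer sees all earlier allocations on the list and knows where blocks start.**

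*Control versus cells certain.* This happens in two ways.
- Both controls are already used. Before position i the probability is C(i−1, 2)/15, that is 0, 0, 1/15, 3/15, 6/15, 10/15. The sum is 20/15 = 1.333 per block (1.333/6 = 22% of allocations).
- All four cell slots are already used. The probability is 1/15 before position 5 and 5/15 before position 6. The sum is 6/15 = 0.400 per block.
- Together 26/15 = 1.733 per block; over ten blocks 17.3 of 60, or 29%.

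*Exact arm certain.* Position 6 always is. Position 5 is when the last two slots belong to the same arm: 3 × (2/6 × 1/5) = 1/5. The sum is 1.2 per block, or 12 of 60 (20%). This requires telling single from double dose as allocations accrue.

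*Best guess of the exact arm.* Enumerating the 90 orders gives 3.367 correct per block, 3.367/6 = 56.1%, against 33.3% by chance.

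If there is one list per centre, the last blocks may be incomplete. Assuming 20 patients per centre, each list has three full blocks plus two patients, who are never predictable. The totals are then 9 × 1.733 = 15.6 (26%) and 9 × 1.2 = 10.8 (18%).

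**Case B: one pooled list, three equal centres (assumed), staff see only their own centre.** Each earlier patient is seen with probability 1/3, and the observer is still allowed to know the block boundaries.
- Exact arm certain: four particular patients must all have been seen, so 0.20 × (1/3)^4 = 0.20/81 = 0.25%. Simulation gives 0.26%, so about 0.3%.
- Control versus cells certain: 0.2222 × (1/3)^2 + 0.0667 × (1/3)^4 = 0.0247 + 0.0008 = 2.6%.
- Best guess of the exact arm (simulation): about 39%.

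**Illustrative bias.** Suppose staff enrol a patient whose expected LVEF change is 1 point higher when the remaining share of cell slots exceeds 2/3, 1 point lower when it is below 2/3, and unshifted when equal. Over the 90 orders the mean shift is +0.267 in each cell arm and −0.533 in control. Cells minus control is 0.267 + 0.533 = 0.80 points; double minus single is 0.267 − 0.267 = 0. In Case B the same rule gives about 0.27. The +1/−1 shift is assumed; nothing in the article supplies it.

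**Effect of random block sizes (simulation, Case A, observer knows the set of possible sizes).**

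| Sizes | Control vs cells certain, of 60 | Exact arm certain, of 60 | Best guess right | Illustrative bias |
|---|---|---|---|---|
| 6 only | 17.3 (29%) | 12.0 | 56% | 0.80 |
| 3, 6, 9 | 3.6 (6%) | 2.3 | 55% | 0.76 |
| 6, 9, 12 | 2.4 (4%) | 1.5 | 52% | 0.67 |

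The percentages are counts over 60: 3.6/60 = 6%, 2.4/60 = 4%. Varying the size removes most of the certainty but little of the guessing advantage while the set is known.

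**The case against.** The strongest objection is that the larger figures depend on something the article does not state. Three hospitals use a web-based service; nothing says that one team enrols at all of them, that allocations are shared, or that lists are kept by centre. Being in one city is not evidence of sharing. In Case B there is almost no certainty and only a small guessing advantage. This stands, so the result has to be given as a range.

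Other points that stand:
- Single and double dose have the same first infusion, and the second comes about 10 days later. The 20% and 56% figures, which need all three arms to be told apart at once, may be too high even for a shared team. The 29% figure does not depend on this.
- A reader might take 0.8 points as an estimate of bias to set against the planned 3-point difference. The article does not support that: the shift is invented and assumed to be applied at every informative slot.
- A reader might infer that the double-versus-single comparison, the stated aim of the trial, is compromised. Steering on control versus cells shifts both cell arms equally.
- The publication date is not shown, so the number of allocations still to come when staff could read the block size is unknown.

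It can also be said that an article leaves list structure and access to the full protocol, and that a fixed block is a common and valid choice. That is fair for what is unstated, and no omission is claimed here. The single size, its disclosure during recruitment and the restriction of blinding to assessors are all stated.

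**Conclusion.** The concern holds as an avoidable risk of selection bias in the cells-versus-control comparisons. Control versus cells is certain for about 29% of allocations if staff see every earlier allocation on the list, and for about 2.6% if there is one pooled list and staff see only their own of three equal centres. The corresponding exact-arm figures are up to 20% and about 0.3%. The article does not show where between these the trial lies.

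The conclusion assumes that controls have no infusion procedure, as the Intervention section describes, although other sections call that arm placebo. It also assumes that staff can work out where blocks begin. It does not show that steering took place, that the web service fails to conceal the next assignment, or that double versus single dose is affected. The case for acting is that exposure may be substantial and the remedy is cheap while allocations remain.

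**What to change.** For all remaining allocations, starting at the next new block, have the web service draw block sizes at random from multiples of 3, keeping 1:1:1. Sizes 6, 9 and 12 do better than a set that includes 3. Withhold both the sizes used and the set of possible sizes from enrolling staff, and from publication, until recruitment closes. The second part is essential, because the guessing advantage falls only slightly if the set is known.

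The cost is a settings change and a sentence in the protocol, with no additional patients and no change to the analysis. On a single list, arm sizes may differ from 20 by one or two: stopping at 60 leaves 3, 6 or 9 places filled in a last block of 12, and each such cut puts an arm at most two away from its share. The date of the change, and the number of patients allocated before it, must be documented. Allocations already made are not protected.

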### Intervention

The cGMP certified clinical-grad hWJ-MSCs produced by Cell Tech Pharmed Co. Ltd. (Tehran, Iran) are transported to the ward on the infusion day. The hWJ-MSCs were suspended in 0.9% normal saline. A qualified person will issue the certificate of analysis for each batch. The release of cells is in compliance with product specifications. The shipment will be handled considering validated standard operation protocols.

Forty patients in the two intervention arms will receive one intracoronary dose of 10^7^ WJ-MSCs infusion, and the control group will be administered only the conventional supportive treatment. For 20 patients among those who had received the first dose, the second dose of 10^7^ WJ-MSCs infusion was done within 10 days after the first injection.

A total of 60 patients in the three groups will be randomized in a 1:1:1 pattern to receive two doses of WJ-MSCs (*n* = 20; 2 × 10^7^ cells) or one dose of WJ-MSCs (*n* = 20; 1 × 10^7^ cells) in combination with conventional supportive treatments or conventional supportive treatments alone (*n* = 20).

When the cells are ready for infusion, the patients will return to the cardiac catheterization laboratory. The total number of 10^7^ WJ-MSCs will be infused via intracoronary route. If the activated clotting time is under 200, a weight-based bolus dose of heparin will be used.

Therapeutic 6 Fr guiding catheter will be inserted into the left main artery. Two hundred micrograms of nitroglycerin will be infused via the guiding catheter. Angiography of LAD will be done, and TIMI flow will be documented. 0.014-inch soft-tipped guidewire wire will be inserted into LAD at distal edge of the stent. An over-the-wire balloon will be passed and placed within the stented area. It will be inflated to occlude the vessel. The guiding wire will be removed from the microinfusion device. Infusion syringe will be connected to the infusion catheter, and infusion of MSCs will be initiated at 2.5 ml/min. Occlusion with balloon catheter will be done using low pressure inflation (2–4 bar). Before each cell infusion, total occlusion of the coronary artery will be confirmed by injection of dye in the selected vessel. When one third volume of the cells is infused, the infusion pump will be ceased, and the contrast agent is injected into the guiding catheter to assess the TIMI coronary flow. This will be done again for the second one third volume. When cell infusion is completed, the coronary flow wire will be placed via the microinfusion catheter. After 10 days, this procedure will be repeated for patients in the third group.

